#### Psychopathology

Psychopathology will be measured with the Brief Psychiatric Rating Scale-Expanded (BPRS-E) [72, 73], which evaluates a broad range of psychiatric symptoms. The BPRS-E is often used as measure of symptom outcome in psychiatric populations [74]. The clinician-administered instrument is sensitive to change in symptom severity, is valid [74, 75] and reliable [74, 76], also in patients with dual diagnosis [77].

#### Emotion dysregulation

Emotion dysregulation will be measured with the Difficulties in Emotion Regulation Scale (DERS) [78]. The DERS evaluates clinically relevant emotion regulation difficulties across multiple domains, represented in six subscales: non-acceptance of emotional responses, difficulty engaging in goal-directed behaviour, impulse control difficulties, lack of emotional awareness, limited access to emotion regulation strategies and lack of emotional clarity. The DERS is used extensively as outcome variable in clinical research and has high internal consistency and good test-retest reliability and construct validity [78, 79], also in patients with SMI [80].

### Other secondary outcome measures

Other secondary outcome measures are:interpersonal functioning as measured with the Inventory of Interpersonal Problems (IIP-32) [81],self-esteem as measured with the Self Esteem Rating Scale (SERS-SF 20) [82],anger disposition as measured with the Dimensions of Anger Reactions (DAR) [83],psychological distress as measured with the Kessler psychological distress scale (K10) [84, 85],quality of life as measured with the EuroQol 5D (EQ-5D-5 L) [86] and the Manchester Short Assessment of Quality of Life (MANSA) [87],healthcare costs and productivity losses/gains as measured with the Trimbos/iMTA questionnaire on Costs associated with Psychiatric illness (TiC-P) [88].

### Other variables of interest

#### General patient characteristics

General demographic characteristics such as age, gender, marital status and educational level will be collected at baseline. Furthermore, current DSM-IV diagnosis, total days of hospitalisation, all-cause mortality, Global Assessment of Functioning (GAF) and mental healthcare received by participants will be extracted from the electronic patient record.

#### Context of victimization

For all crimes reported, context information on victimization will be examined with the Safety Monitor. Each crime reported will be followed by an exploration of the most recent incident. The Safety Monitor contains questions on when and where the incident happened, who the perpetrator was and whether the police was informed. For perpetrator we added the answer options ‘friend’, ‘drug dealer’, ‘other patient’ and 'health care worker’ in addition to the existing options.

In addition to the crimes described in the section ‘primary outcome measure’, four new types of crime that were added in the most recent version of the Safety Monitor will be examined. These new types of crime are: identity fraud, sales fraud, hacking and cyberbullying.

To obtain more detailed information on victimization we extended the Safety Monitor with extra questions. For sexual crimes, threats, assaults and robbery we examine what led to the incident, whether the patient used any substances at the time of the incident and, if relevant, why the participant did not inform the police.

#### Likelihood and controllability of victimization

For each crime assessed with the Safety Monitor, questions are added that examine the perceived likelihood and controllability of becoming a victim of this crime. These questions are based on a risk perception study by Jackson [89]. Participants are asked: ‘to what extent do you feel able to control whether or not you become a victim of the following?’ and ‘how likely do you think it is that you will fall victim of each of the following during the next twelve months?’. To obtain conceptual equivalence, three of the researchers independently translated the questions to Dutch and then formed a panel to resolve discrepancies in these forward translations. Subsequently, an independent translator translated the questions back to English. We discussed discrepancies with this translator until we reached consensus. Finally, we successfully pre-tested the questions on 10 patients from our study population.

#### Perpetration

Perpetration will be measured with the extended version of the Safety Monitor. For each crime, participants are asked if they have committed that crime in the last 5 years. If so, participants are asked if and how often they permitted that crime in the last 12 months. Prior to the assessment of perpetration, participants will be reminded of the confidentiality of the assessment.

#### Within-day relationship victimization and substance use

The within-day relationship between victimization and substance use will be examined with the TLFB [62]. First, substance use will be administered with the TLFB, using calendars, as described in the section ‘secondary outcome measures’. Thereafter participants will reconstruct victimization in the past 90 days, following the same procedure, beginning on the day of assessment and working backwards. For each day on which both victimization and substance use are reported, the within-day process will be examined. Participants will be asked to indicate whether they used substances before being victimized, after being victimized, or both. The TLFB has previously been used to assess partner violence and victimization and their within-day relation to substance use [90–93].

#### Post-traumatic stress disorder

The Jellinek PTSD Screening Questionnaire [94] will be included to screen for post-traumatic stress disorder symptoms. If a participant tests positive, post-traumatic stress disorder symptoms are measured using the Posttraumatic Diagnostic Scale (PDS) [95].

#### Cognitive impairment

The Mini-Mental State Examination (MMSE) will be included to screen for cognitive impairment.

#### Client satisfaction with treatment services

The Client Satisfaction Questionnaire (CSQ-8) [96, 97] will be included to measure participants’ satisfaction with their mental health treatment services.

### Observation scales

For each participant in the clinic, two observation scales will be independently administered by two out of eight nurses, who are not otherwise involved in the SOS training or research. Social functioning will be measured with the Personal and Social Performance scale (PSP) [98]. Aggressive and social behaviour will be measured with the Observation Scale for Aggressive Behaviour (OSAB) [99], which consists of the subscales: irritation/anger, anxiety/gloominess, aggressive behaviour, antecedent (to aggressive behaviour), sanction (for aggressive behaviour) and social behaviour. Due to practical reasons, the observation scales will only be administered for hospitalized participants.

### Evaluation of treatment

After each training session, the SOS-trainers will fill in a session evaluation form in which they note to what extent they followed the instructions in the SOS training manual (scale 1–10) and which participants were present, including a mark (scale 1–10) for effort.

After completing each module of SOS training, participants randomized to CAU + SOS training will fill in a questionnaire to evaluate that module. Each evaluation contains the questions: ‘how much fun was this module to you?’ and ‘how helpful was this module to you?’ (both scale 0–10). Subsequently, participants rate three module-specific skills on a scale from 0 to 100, with 0 being ‘I did not improve on this at all’ and 100 being ‘I improved on this a lot’. Finally, participants will rate how much they improved on self-confidence and on controllability of becoming a victim of crime, due to following this module (scale from 0 to 100).

### Data analysis

#### Sample size calculation

A priori sample size calculations were performed using G*power 3.1.9.2. We are the first to explore effects of an intervention to reduce victimization in this target group, which makes it impossible to provide an exact estimate of effect size for the main outcome measure in this sample. In order to be able to detect a 20 % difference in treatment response between the two trial arms (50 % treatment response in SOS training + CAU versus 30 % treatment response in CAU) with α = .05 and power = .80, the total sample size should be at least 186 (N CAU + SOS training = 93, N CAU = 93). Since a drop-out of 25 % can be expected in this target group we aim to include 250 participants.

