### Interventions

#### Self-wise, Other-wise, Streetwise (SOS) training

The experimental add-on intervention, SOS training, is a 12 session group-based training [47]. Sessions take place twice a week and take 75 min. Each session utilizes learning techniques such as role playing, visual material, group discussions and sharing experiences. The trainers create a safe and respectful environment. Participants can give each other tokens of appreciation during every session, in order to reinforce desirable behaviour. These tokens are cards with coloured stars. By using the tokens, participants learn to reinforce and support each other. Furthermore, the tokens stimulate the participants to listen to and interact with each other. The training comprises 3 modules, *Self-wise, Other-wise* and *Streetwise.* Each module consists of 4 sessions. There is no specific order in which participants follow these modules.

The module *Self-wise* involves a transdiagnostic emotion regulation skills training. Emotion regulation refers to the ability to monitor, evaluate and modify emotional reactions to accomplish one’s goals [48]. Emotion dysregulation is a predictor of victimization [12, 49–51]. Lack of emotional awareness, for instance the inability to recognize and interpret fear cues, impairs risk perception [12, 52]. Poor risk perception increases the risk for victimization [49, 52]. Emotion dysregulation, especially impulsivity, also increases the likelihood of entering a risky situation and makes it more difficult to leave or adequately cope with a dangerous situation [12, 52]. Even small increases in emotion regulation can impact victimization risk substantially [12]. Since no evidence-based emotion regulation skills training is available for our target group, the content of *Self-wise* is inspired by elements of affect regulation therapy for major depressive disorder [42], anger management training for people with intellectual disabilities [43], skills training in affect and interpersonal regulation for patients with posttraumatic stress disorder related to childhood abuse [44] and the system training for emotional predictability and problem solving for patients with borderline personality disorder [45]. *Self-wise* is a new, simplified emotion regulation skills training suitable for patients with dual diagnosis, based on the principles of these interventions.

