#### Therapists

SOS training will be implemented in the treatment programs of an addiction-psychiatry dual diagnosis clinic and an addiction-psychiatry outpatient care facility of Arkin Mental Health Care, division Mentrum. Arkin is an Amsterdam-based public mental health care treatment facility. Eight employees are selected to be trained to deliver the intervention. These SOS-trainers work in various positions, for instance as psychologist, nurse or social worker. All have ample experience in working with psychiatric patients with substance use disorders and are motivated to implement this new intervention. The SOS-trainers will follow a detailed training manual which describes each training session. Each session will be led by an SOS-trainer accompanied by an SOS-co-trainer.

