#### Effectiveness

Primary data analyses will be performed in accordance with the intention-to-treat paradigm. In addition, per protocol analyses will be conducted. Missing data will be addressed using multiple imputation. Statistical significance will be set at α < .05, based on two-sided tests. The effect of treatment in terms of the primary and secondary outcome variables will be analysed with generalized linear mixed model regression analysis (GLMM) with adequate link functions, taking into account distributional characteristics of the data.

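### The sample size makes no allowance for correlation within SOS training groups, so the stated 80% power falls short for any material within-group correlation

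*Protocol article*

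**What the plan says.** Sample size calculation (Protocol article) assumes "50 % treatment response in SOS training + CAU versus 30 % treatment response in CAU", "with α = .05 and power = .80", and concludes that "the total sample size should be at least 186 (N CAU + SOS training = 93, N CAU = 93". One adjustment follows: "Since a drop-out of 25 % can be expected in this target group we aim to include 250 participants". The section mentions no group size, ICC or design effect.

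The intervention section states: "The experimental add-on intervention, SOS training, is a 12 session group-based training". It describes role play, discussion and mutual reinforcement with tokens as part of the method, and leaves the order of the three modules free. Under Therapists, eight employees are trained to deliver SOS, and "Each session will be led by an SOS-trainer accompanied by an SOS-co-trainer". According to Design and Trial flow, randomization is of individuals and only one arm receives SOS.

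Effectiveness plans a generalized linear mixed model "with adequate link functions, taking into account distributional characteristics of the data". It names no random effect for training group or trainer and excludes none.

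**The concern.** This is an individually randomized, partially nested design. SOS participants share group members and trainers, and the control arm has no SOS groups. Where interaction between participants is part of how a treatment is meant to work, positive correlation of outcomes within groups is plausible. It would inflate the variance of the SOS arm's response rate, while the calculation treats all 186 participants as independent.

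At stake is the power claimed for the primary comparison. An analysis plan can choose the right model, but it cannot supply power that the sample size did not provide for. A second consequence, an inflated type I error, would follow only if the final model omitted the group effect.

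**Working it through.** **Inputs from the document.** Response 0.50 versus 0.30, α 0.05, power 0.80, 93 per arm, 25% drop-out, 250 enrolled (Sample size calculation); "Statistical significance will be set at α < .05, based on two-sided tests" (Effectiveness).

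**Inputs assumed.** Analysed participants per SOS group, m = 4 to 12; ICC = 0.01 to 0.10. Neither is in the document.

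**Step 1: reproduce the plan's figure.** With independent observations and pooled variance under the null (mean rate 0.40):

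n = [1.960·√(2·0.40·0.60) + 0.8416·√(0.50·0.50 + 0.30·0.70)]² / 0.20²
= [1.358 + 0.571]² / 0.04 ≈ 93 per arm, 186 in total.

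Power at 93 per arm is 0.800. The stated figure is matched exactly, so it contains no allowance for clustering.

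**Step 2: slack in the enrolment target.** 250 × 0.75 = 187.5 completers against 186 needed, which leaves 1.5 to spare. At 94 per arm the independent-data power is only 0.804. The enrolment margin does not absorb clustering.

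**Step 3: design effect in the SOS arm only.** DE = 1 + (m − 1)·ICC, with the control arm left at 1:

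- SE under the null = √[0.24·(DE + 1)/93]
- SE under the alternative = √[(0.25·DE + 0.21)/93]
- Power = Φ{(0.20 − 1.960·SE null)/SE alternative}

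Example with m = 8 and ICC 0.05: DE = 1.35; SE null = √(0.564/93) = 0.0779; SE alternative = √(0.5475/93) = 0.0767; power = Φ(0.0474/0.0767) = 0.731.

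Power at 93 analysed per arm:

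| m | ICC 0.01 | ICC 0.05 | ICC 0.10 |
|---|---|---|---|
| 4 | 0.794 | 0.770 | 0.741 |
| 8 | 0.786 | 0.731 | 0.670 |
| 12 | 0.778 | 0.696 | 0.609 |

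For scale only: holding 80% at m = 8 and ICC 0.05 would take 110 per arm, that is 220 completers, or 220/0.75 ≈ 294 enrolled.

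**Step 4: conditional type I error.** If the final model left out the group effect, the actual two-sided error would be 2·[1 − Φ(1.960·√(2/(DE + 1)))]:

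| m | ICC 0.01 | ICC 0.05 | ICC 0.10 |
|---|---|---|---|
| 4 | 0.052 | 0.059 | 0.068 |
| 8 | 0.054 | 0.071 | 0.092 |
| 12 | 0.056 | 0.083 | 0.115 |

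Both tables treat groups as fixed and use a normal approximation.

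**The case against.** **The correlation may be small.** The outcome is self-reported crime over the 12 months before the last interview, which itself falls 12 months after training ends, and it includes bicycle theft, burglary and vandalism. Nothing in the document supports an ICC of 0.05 to 0.10 for such an outcome. At ICC 0 the 80% stands, and at ICC 0.01 the loss is only 0.6 to 2.2 points. This stands. A reader might infer that the 80% is certainly missed, but the document does not support that.

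**The analysis may already handle groups.** A reader might also infer that the planned standard errors are too small. The document does not support that either: a mixed model can carry a group effect, and an article commonly leaves the random-effects structure to an analysis plan. The figures in Step 4 are therefore conditional. Similarly, Cost-effectiveness calculations does not name the bootstrap's resampling unit, so it cannot be said to ignore groups.

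**Groups are not fixed.** With free module order, a participant may meet different peers in each module, so a fixed-group design effect is an approximation. This stands, but changing membership does not restore independence, and the shared trainers remain. Both arms may also attend other psychosocial therapy, but the SOS groups exist in one arm only.

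**Other uncertainty is as large.** The article concedes that the effect size cannot be estimated exactly. At 93 per arm, 49% versus 30% gives power 0.76 and 48% versus 30% gives 0.71, which is comparable with the mid-range clustering scenario. This argues for modest severity. It does not justify leaving a structural feature of the design out of the calculation.

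**Conclusion.** The point holds for the sample size. The 186 rests on independence between participants, which the article neither states nor defends and which its own description of SOS makes doubtful. Power is below 80% for any material within-group correlation: from 0.79 down to 0.61 over the assumed range, and 0.73 at 8 per group with ICC 0.05. These figures depend on assumed group sizes and ICCs and on treating groups as fixed. The arithmetic of the 186 and of the drop-out inflation is correct in itself.

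On the analysis, the conclusion is only conditional: two-sided type I error would be about 5.2% to 11.5% over the same range if the group effect were omitted. The point is worth correcting before analysis, but it does not undermine the trial.

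**What to change.** - **Sample size calculation:** restate the power at N = 250 as a range, with a design effect in the SOS arm only, and label group size and ICC as assumptions.
- **Effectiveness:** specify that the mixed model carries a random effect for training group in the SOS arm, absent in the control arm, with small-sample degrees of freedom. Assign each SOS participant to the group scheduled at allocation. The session forms record only who was present, so they give no group to those who never attend, yet intention-to-treat keeps them. Note that free module order makes the grouping approximate.
- **Cost-effectiveness calculations:** name the resampling units, using the same groups in the SOS arm.

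The cost is some wording and one group identifier per SOS participant, which should be kept from the blinded outcome assessors. The stated power becomes slightly less favourable and the intervals slightly wider. No extra patients are required, and the change describes the power accurately without restoring it to 80%.

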#### Effectiveness

Primary data analyses will be performed in accordance with the intention-to-treat paradigm. In addition, per protocol analyses will be conducted. Missing data will be addressed using multiple imputation. Statistical significance will be set at α < .05, based on two-sided tests. The effect of treatment in terms of the primary and secondary outcome variables will be analysed with generalized linear mixed model regression analysis (GLMM) with adequate link functions, taking into account distributional characteristics of the data.

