### Randomization and treatment allocation

Participants will be allocated to CAU + SOS training or CAU by an independent researcher using a computer-generated block randomization schedule. Randomization will be stratified by two prognostic factors: treatment centre (clinic/outpatient care) and victimization in the year prior to baseline (yes/no). Block size varies randomly. To prevent selection bias, the research coordinator and outcome assessors are denied access to the randomization schedule and are blind to block size and order.

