### Primary outcome measure: victimization

Victimization will be measured with the Dutch version of the Safety Monitor (in Dutch: Veiligheidsmonitor, VM section 4), developed by the Dutch Ministry of Security and Justice [60]. The Safety Monitor is an instrument used by Statistics Netherlands (CBS) to measure victimization on a large scale (almost 80 thousand cases a year). It is an adequate self-report instrument that strongly resembles the International Crime Victimization Survey (ICVS) [61]. Section 4 of the Safety Monitor assesses victimization of 11 different crimes, subdivided in three categories:violent crimes, consisting of: sexual crimes, threats and assaults;property crimes, consisting of: burglary, theft from car, car theft, motor vehicle theft, bicycle theft, robbery and theft of other property;vandalism;

The Safety Monitor examines whether participants experienced each specific crime in the last 5 years. If so, they are asked whether they experienced that crime in the last 12 months. For each crime reported, participants are asked how frequently they experienced that crime in the last 12 months.

The primary outcome measure is treatment response (yes/no), defined as either no victimization at T3 or at least a 50 % reduction in incidents of victimization at T3 compared to T0. Since there are no previous randomized controlled trials available that aimed to reduce victimization in this target group, our treatment response criteria are based on experts opinions. Mental health care professionals working with dual diagnosis patients indicated a 50 % reduction in incidents of victimization as a clinically relevant and achievable goal.

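### The one mixed model named for all outcomes does not fit a primary outcome with a single yes/no value per participant; the primary model should be stated separately, with the two stratification factors in it

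*Protocol article*

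**What the plan says.** All references are to the protocol article.

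- **Primary outcome measure: victimization.** "The primary outcome measure is treatment response (yes/no"). A participant counts as a responder with no incidents at T3, or with an incident count that has at least halved since T0. The counts come from the Safety Monitor, in which "participants are asked how frequently they experienced that crime in the last 12 months".
- **Measurements, Table 1.** The Safety Monitor is scheduled at T0 and T3 and at no other visit. Most secondary scales are scheduled at three or four visits.
- **Effectiveness.** "The effect of treatment in terms of the primary and secondary outcome variables will be analysed with generalized linear mixed model regression analysis (GLMM"). The same sentence leaves the choice of link open, to suit each outcome's distribution. No random effect and no covariate is named for any outcome.
- **Randomization and treatment allocation.** "Randomization will be stratified by two prognostic factors: treatment centre (clinic/outpatient care) and victimization in the year prior to baseline (yes/no").
- **Sample size calculation.** The trial is sized on a difference between two response proportions, 50 % against 30 %, with α = .05 and power .80. This gives 186 evaluable participants and 250 recruited.

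**The concern.** A mixed model separates variation within a unit from variation between units. The repeated secondary scales allow this, with participant as the natural unit. The primary outcome does not: response uses up both Safety Monitor assessments, so there is one binary value per participant and nothing varies within a participant. The article nevertheless puts it under the same model class as the repeated scales. If an analyst carries the participant random intercept over, the data cannot determine its variance. The reported odds ratio is then conditional on whatever value the software settles on or the analyst fixes.

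A smaller matter concerns the strata. The article describes treatment centre and prior-year victimization as prognostic. The second is also tied to the endpoint: someone with no incidents at T0 can respond only by having none at T3. Stratified allocation removes chance imbalance in these factors. An analysis that leaves them out does not credit that, so its standard error tends to be somewhat too large. What is at stake is how the effect size is reported and a modest amount of power, not the validity of the treatment test.

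**Working it through.** **1. The plan's own figure.** Inputs from Sample size calculation: 50 % and 30 %, power .80; two-sided α = .05 from Effectiveness. With pooled variance and no continuity correction,

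n per arm = [1.96 × √(2 × 0.4 × 0.6) + 0.8416 × √(0.5 × 0.5 + 0.3 × 0.7)]² / 0.20² = (1.358 + 0.571)² / 0.04 ≈ 93.

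The total is 186, as stated. With 25 % drop-out, 186 / 0.75 = 248, which the article rounds up to 250. Both figures reproduce.

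**2. Can a participant random intercept be estimated?** Take 93 per arm with responders near the planned rates: 28/93 (30.1 %) in CAU and 47/93 (50.5 %) in SOS + CAU. A logistic model with arm and a participant random intercept has three parameters: intercept, arm effect and random-intercept SD. The data supply two proportions. For each fixed SD the likelihood was integrated by Gauss-Hermite quadrature and maximised:

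| Random-intercept SD | Maximised log-likelihood | Treatment odds ratio |
|---|---|---|
| 0 | -121.352 | 2.37 |
| 0.5 | -121.352 | 2.49 |
| 1 | -121.352 | 2.82 |
| 2 | -121.352 | 4.10 |
| 3 | -121.352 | 6.42 |

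The row at SD 0 is ordinary logistic regression: (47/46) / (28/65) = 2.37. Every SD fits the two proportions exactly, so the data cannot choose among them.

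**3. What does not move.** Without arm, the model has to fit only the pooled 75/186, which it also does exactly at any SD: 75 × ln(75/186) + 111 × ln(111/186) = -125.419. The likelihood-ratio statistic is therefore 2 × (125.419 - 121.352) = 8.13 at every SD. The difference in fitted proportions is likewise 19/93 = 20.4 points at every SD. Only the conditional odds ratio is arbitrary.

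**4. The strata.** The article gives no association between the strata and response, so one has to be assumed. The simulation used logistic regression with and without the two strata, 2,500 runs per scenario, 184 or 188 participants (stratum sizes rounded), and arms balanced within strata. Marginal response was held at 30 % and 50 % for power, and at 30 % in both arms for type I error. Assumptions: 50 % or 70 % victimized at baseline; half the participants in each centre; stratum odds ratios of 1, 2, 3 and 5 for prior-year victimization, and 1 and 2 for centre.

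| | Without strata | With strata |
|---|---|---|
| Power | 0.79 to 0.82 | 0.79 to 0.87 |
| Type I error | 0.036 to 0.050 | 0.044 to 0.056 |

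The gain in power, by odds ratio for prior-year victimization:

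- Odds ratio 1 for both factors: about 0 points (0.788 to 0.792).
- Odds ratio 2 or 3: about 2 to 4 points (for example 0.797 to 0.820 at odds ratio 3 with no centre effect).
- Odds ratio 5: about 4 to 5 points (for example 0.801 to 0.853 with 70 % victimized).

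The Monte Carlo standard error of a 5 % rejection rate is √(0.05 × 0.95 / 2,500) = 0.004, so differences of a few thousandths in type I error are noise.

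**The case against.** The strongest reply is that the article never places the random effect at participant level. One sentence covers all outcomes, most of them repeated, and leaves room to suit the model to each. A mixed model whose random effect cannot be estimated can reduce to ordinary logistic regression. This stands in part: the analysis is not impossible to run, and the result in step 2 applies to one specification among several. But the article names no other grouping factor, and participant is the natural unit for the other outcomes. A mixed model of the T0 and T3 incident counts could be fitted, but it would not analyse the stated response endpoint or match the 50 % against 30 % planning. The freedom to choose a link function does not help, because the link is not the difficulty.

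The second reply is that covariates belong in an analysis plan that is not shown. That stands. A reader might infer that the trial will discard its strata, but the Effectiveness section neither includes nor excludes them, and silence in a condensed article is not exclusion. A reader might also take the strata to be strongly prognostic. The article says only that they are prognostic and gives no figure; the size and direction of any association with response are unknown.

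Third, a reader might infer that the trial's significance test is compromised. Step 3 shows that it is not.

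**Conclusion.** The point holds in a limited form. The article does fix a model class for the primary outcome, and that class does not suit an endpoint with one binary value per participant. If the random effect is at participant level, its variance is unidentified and the conditional odds ratio is arbitrary: 2.37 to 6.42 for the same data over SDs of 0 to 3. The likelihood-ratio test and the difference in proportions are untouched. This part rests on the visit schedule and the endpoint definition, plus the condition about the level of the random effect, which the article leaves open.

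On the strata the point is a recommendation, not an error found. An analysis without them would be valid and at most slightly conservative. The cost of about 0 to 5 power points rests entirely on the assumed stratum effects and is nil if the strata do not predict response. For a trial planned at 80 % power this is modest but worth having. The sample size of 186 stands.

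**What to change.** State the primary analysis in its own sentence: logistic regression of T3 response, one record per participant, with arm, treatment centre and prior-year victimization (yes/no) as predictors. Beside the odds ratio, report a standardized risk difference with its confidence interval, since the sample size is set on the difference in response proportions. Keep participant-level random effects for outcomes measured at several waves.

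The cost is a few lines of wording. Both factors are known before randomization because allocation is stratified by them, so no new data are needed and the required 186 does not rise. Further covariates or a random effect for training groups are matters of preference and are not needed to settle this point.
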